### 1.2 Secondary Objectives

The secondary outcomes include the Good Birth Outcome rate, cumulative pregnancy rate, cumulative pregnancy loss rate, multiple pregnancy rate, duration of pregnancy, birth weight, cumulative incidence of maternal and neonatal complications (including fetal anomalies) and number of transfers to achieve live birth.

The secondary hypotheses are as follows:

- 1) PGS will be more likely to achieve a Good Birth Outcome than IVF.
- 2) PGS will reduce the rate of pregnancy loss.
- 3) The incidence of other maternal and neonatal complications will be comparable between PGS and IVF groups.
- 4) The rate of multiple pregnancy will be low and comparable between PGS and IVF groups
- 5) The birth weights will be comparable between babies delivered from PGS and IVF.
- 6) PGS will reduce the number of embryo transfers to achieve live birth.

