### 6.2.3 Intervention Discontinuation Evaluations

After randomization, further participation in the study will be discontinued in the following situations: a) no euploid embryo is obtained in patients assigned to the PGS group after NGS test; b) Subjects who run out of the protocol-specified embryos; c) Subjects who do not complete transfers of the protocol-specified embryos within 1 year after randomization. Subjects who conceive will be followed to the termination of the pregnancy.

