## 9 STATISTICAL CONSIDERATIONS

### 9.1 General Design Issues

This is a multicenter randomized controlled trial comparing the benefit and safety of PGS and conventional IVF in women with good prognosis. Subjects will be randomly assigned to 2 parallel groups with 1:1 ratio. This study is designed as a non-superiority study to test the following primary and secondary hypothesis.

- a) The primary hypothesis is that PGS will result in a similar cumulative live birth after up to 3 transfers within 1 year after randomization compared with conventional IVF.
- b) The secondary hypotheses are as follows:
  - 1) PGS will be more likely to yield a Good Birth Outcome.

- 2) PGS will reduce the rate of pregnancy loss.
- 3) The incidence of other maternal and neonatal complications will be comparable between PGS and IVF groups.
- 4) The rate of multiple pregnancy will be comparable between PGS and IVF groups
- 5) The birth weight will be comparable between babies resulted from PGS and IVF.
- 6) PGS will require fewer embryo transfers before achieving live birth.

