### 9.2.2 Secondary outcomes:

The secondary outcomes include the Good Birth Outcome rate (defined as a live birth of an infant born at  $\geq 37$  weeks, with a birth weight between 2500 and 4000g and without a major congenital anomaly), cumulative pregnancy rate, cumulative pregnancy loss rate, multiple pregnancy rate, duration of pregnancy, birth weight, cumulative incidence of maternal and neonatal complications, and number of embryo transfers to achieve live birth.

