## 9.3 Sample Size and Accrual

Given the possibility of false positive and the decision of not transferring mosaic embryos which are probably to develop into live birth, we assume that the cumulative live birth rate after transferring PGS-selected euploid embryos will be similar with that after serially transferring all the 3 untested blastocysts. This study is designed as a non-superiority study. It is estimated the cumulative live birth rate after 3 single embryo transfers is 65% in the IVF control group. We set a non-superiority margin at an absolute difference of 7% to retain approximately 90% of the clinical effect of the control group. To be 80% certain that the upper limit of a one-sided 95% confidence interval (CI) of absolute difference between groups to reject null hypothesis that PGS is superior to conventional IVF, 575 pa-

tients were required in each group. In consideration of 5% drop-out rate, a total of 1208 subjects will be enrolled. At present, 8 centers have volunteered and qualified to participate in subjects' enrollment. It is planned that each center will approximately enroll 150 subjects.

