#### 9.5 Data Analyses

The primary analysis will be performed in accordance with the principle of intent-to-treat. Continuous variables will be described as mean  $\pm$  standard deviation for the normally distributed variables and as median and range for the non-normally distributed variables. Category variables will be presented as frequency and percentage. The differences in the cumulative live birth rate in the two treatment arms will be compared by absolute risk difference and its 95% confidence interval (CI). The relative risk and its 95% CI will also be calculated. Non-superiority of PGS to IVF will be considered to be established if the upper limit of the 95% CI of absolute risk difference was shown to lie below the non-superiority margin of 7%.

The differences in the secondary outcomes such as rate of Good Birth Outcome, cumulative pregnancy rate, cumulative pregnancy loss rate, multiple pregnancy rate obstetric and neonatal complications will be tested by Person chi-square analyses. The absolute difference and 95%CI as well as relative risk and 95% CI will also be calculated. The difference between duration of pregnancy, birth weight and times of embryo transfer will be tested by student t test and non-parameter test if necessary.

The tertiary outcomes such as the rates of pregnancy, pregnancy loss and live birth after the first transfer will be analyzed with Pearson chi-square test. Cost-effectiveness analysis will be done by decision analytic model with TreeAge Pro 2014 (2014 Version; TreeAge

software). Cost effectiveness is defined as an incremental cost effectiveness ratio (ICER). The ICER for live birth was calculated as the difference in cost between two treatment groups divided by the difference in live birth rates between the two groups. The secondary analysis will be performed according to per-protocol analyses. The primary and secondary outcomes will be compared according to actual treatment that subjects received and among subjects who complete embryo transfer(s).

Subgroup analyses will be performed according to different stimulation protocol (e.g. agonist long, agonist short, and antagonist protocol), different endometrial preparation protocol for FET (e.g. natural ovulation cycle and artificial cycle), age groups (e.g. 20~30 group, 30~35 group and >35 group), with or without history of recurrent spontaneous abortion.

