**Final statistical analysis**

Given the possibility of false positive and the decision of not transferring mosaic embryos which are probably to develop into live birth, we hypothesized that the cumulative live birth rate after the transfer of PGT-A-selected euploid blastocysts is not clinically better than that after serially transferring all the 3 untested blastocysts. This study was therefore designed as a non-superiority study. It was estimated the cumulative live birth rate after 3 single embryo transfers was 65% in each group. To be 80% certain that the upper limit of a one-sided 95% confidence interval (CI) would exclude a difference in favor of the PGT-A group by more than 7%, 575 patients were required in each group. In consideration of 5% drop-out rate, a total of 1,208 patients were needed.

Continuous baseline characteristics of PGT-A and IVF groups were represented as means  $\pm$  SD, and between-group differences were compared by Wilcoxon rank-sum test. Categorical variables were represented as frequencies and percentages, and compared by chi-square test. Fisher's exact test was performed for the number of frequencies less than five. Non-superiority test was used to evaluate the absolute rate differences with a two-sided 90% CI for the primary hypothesis only. Other categorical variables were analyzed by estimation of absolute rate differences and relative rates with a two-sided test. Kaplan-Meier curves were used for the time to live birth. We also conducted secondary analyses based on actual treatment that the patients received, the initial, secondary and third embryo transfer in PGT-A and IVF groups. Subgroup analyses were performed according to different endometrial preparation protocol for frozen embryo transfer and age groups. Two-sided P value of  $<0.05$  were considered significant. All analyses were performed using SAS software (version 9.4, SAS Institute).

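### The planned t test on transfer counts cannot judge hypothesis 6: at the protocol's own euploid shares it would favour PGS even if sequencing predicted nothing

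*Combined protocol and SAP*

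**What the plan says.** Section 1.2 states the hypothesis as "PGS will reduce the number of embryo transfers to achieve live birth", and section 9.1 as "PGS will require fewer embryo transfers before achieving live birth". Section 9.2.2 lists the outcome as "number of embryo transfers to achieve live birth". The only test that section 9.5 gives for it is "times of embryo transfer will be tested by student t test and non-parameter test if necessary".

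No section says whether the count is taken over all randomised women, women with at least one transfer, or women with a live birth. None says what value is given to a woman without a live birth or without a transferable embryo.

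The two arms have different ceilings. Under section 5.1, IVF women have three day-5 blastocysts set aside for the first three transfers. PGS women have three sequenced and receive the euploid ones; section 5.1.3 adds embryos with failed amplification and holds back mosaics. Under section 6.2.3, participation ends if "no euploid embryo is obtained in patients assigned to the PGS group after NGS test", so zero transfers is a possible PGS result.

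**The concern.** A lower transfer count has two possible sources: live birth comes sooner, or embryos run out sooner. Only the first is the benefit that hypothesis 6 describes, and the planned test cannot tell them apart.

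- **Over all women**, someone with no euploid embryo would contribute the lowest count if scored as zero, although she has no chance of a study live birth.
- **Among women with a live birth**, the groups are selected after randomisation. A PGS woman with one released embryo can only succeed at transfer 1, so late successes are removed from the PGS mean.

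The non-parametric fallback has the same fault, because the problem is the quantity compared and not its distribution.

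At stake is one of the directional benefit hypotheses for PGS. The trial could report fewer transfers as an advantage when the cause is lost opportunity.

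**Working it through.** **The plan's own figure.** With 65% in both arms, a 7-point margin, one-sided 5% and 80% power: n = (1.645 + 0.842)² × 2 × 0.65 × 0.35 / 0.07² = 574.1, so 575 per arm. Then 575 × 2 × 1.05 = 1207.5, so 1208 in total and 604 per arm. The plan's figures reproduce. It gives none for the transfer count.

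**Inputs.**
- Control rate (section 9.3): "the cumulative live birth rate after 3 single embryo transfers is 65% in the IVF control group".
- Share of embryos released: about 60% (section 2.1) or 40–56% in top-scoring blastocysts (section 2.2, rationale for morphologic scoring).
- Two-sided 5% level (Final statistical analysis).
- Assumptions: a constant, independent live birth rate per transfer; release unrelated to viability (a test with no predictive value); no effect of biopsy, thaw loss or the one-year limit.

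**Per-transfer rate.** p = 1 − 0.35^(1/3) = 0.2953.

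**IVF arm.** Births at transfers 1, 2, 3: 0.2953, 0.2081, 0.1466 (sum 0.650).
- Mean transfers, all women: 1 + 0.7047 + 0.7047² = 2.20.
- Births only: (0.2953 + 2 × 0.2081 + 3 × 0.1466) / 0.650 = 1.77.

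**PGS arm, 60% released at random.** Released embryos K ~ Binomial(3, 0.6), so P(K≥1), P(K≥2), P(K=3) = 0.936, 0.648, 0.216. Births at transfers 1, 2, 3: 0.2764, 0.1348, 0.0317 (sum 0.443).
- Mean, all women: 0.936 + 0.648 × 0.7047 + 0.216 × 0.4966 = 1.50.
- Births only: (0.2764 + 2 × 0.1348 + 3 × 0.0317) / 0.443 = 1.45.

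**Planned comparison, 604 per arm.**
- All women (SD 0.867 and 0.770): z = 0.701 / √(0.867²/604 + 0.770²/604) = 14.9.
- Births only (393 v 268 women; SD 0.792 and 0.625): z = 0.324 / √(0.792²/393 + 0.625²/268) = 5.9.

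The probability of a significant result favouring PGS is Φ(z − 1.96), above 99.9% for both. Restricting to women with at least one transfer gives 2.20 v 1.60, again above 99.9%.

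**Varying the share released at random** (IVF: 65.0% live birth; means 2.20 and 1.77):

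| Released | PGS live birth | PGS mean, all | PGS mean, births | P(favours PGS), all | P(favours PGS), births |
|---|---|---|---|---|---|
| 40% | 31.4% | 1.06 | 1.29 | >99.9% | >99.9% |
| 60% | 44.3% | 1.50 | 1.45 | >99.9% | >99.9% |
| 80% | 55.4% | 1.88 | 1.61 | >99.9% | 84% |
| 90% | 60.4% | 2.05 | 1.69 | 89% | 31% |
| 95% | 62.8% | 2.13 | 1.73 | 34% | 11% |

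**Variation between women.** If p follows a beta distribution (concentration 2 or 5), with 60% released and 575 per arm, simulation still gives at least 99% for the t test and 98.9% for Mann–Whitney on every denominator. PGS live birth is then 50% or 47%.

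**Does the proposed measure separate the cases?** A perfect test that releases 60% keeps every viable embryo, so its rate per transfer is 0.2953 / 0.6 = 0.492.

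| | After 1 | After 2 | After 3 | Transfers per live birth | Mean transfers, births only |
|---|---|---|---|---|---|
| IVF | 29.5% | 50.3% | 65.0% | 3.39 | 1.77 |
| Worthless test | 27.6% | 41.1% | 44.3% | 3.39 | 1.45 |
| Perfect test | 46.1% | 62.3% | 65.0% | 2.03 | 1.33 |

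The raw count falls for both tests. The cumulative proportions and the ratio improve only for the perfect one.

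**Why the claim rule needs two conditions.**
- *A confidence interval.* After transfer 1 with 60% released, the difference is −0.0189 with SE 0.0260. A higher point estimate for PGS arises with probability Φ(−0.73) = 23%; a 95% CI above zero with Φ(−2.69) = 0.4%. With 80% released these are 46% and 2.0%.
- *A link to the primary outcome.* Suppose 50% of embryos are released and 80% of viable ones kept (0.2953 × 0.8 / 0.5 = 0.472 per transfer). PGS then leads after transfer 1 (41.3% v 29.5%) but ends lower (55.4% v 65.0%).

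**The case against.** **The loss would be visible.** This stands. The primary outcome (section 9.2.1) divides by all women randomised, and section 9.5 reports its difference with a CI. With live birth at 55.4% v 65.0% and 604 per arm, a two-sided 95% CI excludes zero about 93% of the time. Section 2.2 itself warns that PGS may reduce both transfers and live births per woman. A reader might infer that the plan would hide a loss; it would not. But the non-superiority criterion is also met when PGS lowers live births, and nothing ties hypothesis 6 to the primary result.

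**Better analyses are already planned.** Live birth after the first transfer is a tertiary outcome (sections 9.2.3 and 9.5). The Final statistical analysis adds analyses of the first, second and third transfers and Kaplan–Meier curves for time to live birth. This stands too, so most of the fix is already in hand. None of these is assigned to hypothesis 6, and the Summary of changes does not withdraw the t test.

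**Counting over all women is an unlikely reading.** The outcome's name points to women with a live birth, and the documents do not say that a woman without a euploid embryo scores zero. That is fair, and the births-only results are therefore shown throughout; they fail at the documents' euploid shares as well.

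**A lower count may be a true benefit.** With a perfect test it falls from 1.77 to 1.33 among births, and the conclusion would be right. The fault is lack of specificity, not a test that always misleads.

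**No rule says when hypothesis 6 is declared.** Correct, but the hypothesis is directional and this is the only test attached to it.

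**Conclusion.** The concern holds within limits. At released shares of 40–60%, and under the assumptions above, a test with no predictive value would be found to reduce transfers with more than 99.9% probability, over all women or among births only. At 60% released, live birth falls by 20.7 points (65.0% to 44.3%).

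Two stronger readings are tempting and unsupported. One is that the count falls whenever embryos are withheld. The result depends on release being unrelated to viability; a test that withheld only viable embryos, 20% of them, would leave the mean over all women about unchanged (2.21 v 2.20). The other is that a false finding is almost certain in any case. On the births-only reading it is 84% with 20% withheld, 31% with 10% and 11% with 5%.

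This is more than a missing definition, because each available denominator gives the misleading result at the documents' euploid shares. It concerns one secondary hypothesis and leaves the primary analysis untouched.

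**What to change.** In section 9.5, replace the t test for this outcome:

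- Judge hypothesis 6 on the cumulative proportion of all randomised women with a live birth after study transfers 1, 2 and 3, with risk differences and 95% CIs. Women with no transferable embryo or no live birth stay in the denominator as not achieved.
- Regard the hypothesis as supported only if the 95% CI at one pre-specified early transfer number excludes zero in favour of PGS.
- Always report that result beside the primary cumulative live birth difference, and claim no transfer-saving benefit if that difference shows a loss with PGS. The SAP should define a loss in advance; a 95% CI wholly below zero is one option.
- Report total study transfers divided by total live births in each arm, with a bootstrap CI, as support. Show raw transfer counts descriptively only.

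The cost is SAP wording: the planned outcome and per-transfer analyses already need the transfer and birth data, and no clinical procedure changes. The downside is that hypothesis 6 becomes harder to claim.

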### **Sample Size and Population**

03/07/2017

We aim to enroll good-prognosis women who are undergoing their first cycle of IVF. The targeted population is women age 20 to 37y, with 3 or more good-quality blastocysts obtained on day 5 of embryo culture. The exclusion criteria are women with a uterine cavity abnormality or women who plan to undergo preimplantation genetic diagnosis (PGD). Given the likelihood of a high proportion of mosaic embryos in the PGS group and our decision to not transfer mosaic embryos (which are unlikely to achieve live birth and have an unknown risk-benefit ratio), we assume that the cumulative live birth rate after the transfer of PGS-selected euploid blastocysts will unlikely exceed that after serially transferring all the 3 untested blastocysts. This study is therefore designed as a non-superiority study. It is estimated the cumulative live birth rate after 3 single embryo transfers is 65% in each group. To be 80% certain that the upper limit of a one-sided 95% confidence interval (CI) would exclude a difference in favor of the PGS group by more than 7%, 575 patients are required in each group. In consideration of 5% drop-out rate, a total of 1208 subjects will be enrolled. The randomization will be stratified by study site. Blocked randomization will be used with dynamic block size. The random number sequence will be generated by the data coordinating center and will be unknown to all investigators. The randomization will be performed on day 5 of embryo culture via a central online randomization system. At present, 8 centers have volunteered and qualified to participate in subjects' enrollment. It is planned that each center will approximately enroll 80 subjects.

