### **Limitations of published clinical trials and urgent need of high-quality RCTs**

Large heterogeneity exists among these clinical trials, such as different genetic platforms, different biopsy methods and stage, and the number of RCTs published so far is rather limited, which undermines the credibility of the conclusions drawn from meta-analyses and systematic reviews.

Most importantly, critics of PGS claimed that the efficacy of published clinical trials is compromised for several important limitations of study quality and design. First, concerns have been expressed about the improper design of RCTs to date, including non-comparable interventions, lack of allocation concealment, large loss to follow-up, and inappropriate outcome measures, for example not reporting live birth rates or perinatal complications. Second, in most published RCTs, only a single transfer cycle was included and the results of subsequent FETs were not counted. Increasingly national ART registries are requiring cumulative live birth rates as the ultimate measure of cycle success to avoid gaming the system which in the past rewarded primarily pregnancies that occurred after the initial fresh transfer. Third, the pregnancy outcomes were analyzed with the unit of per transfer cycle, rather than with per cycle started or per woman with an intent-to-treat principle. The implantation rate (IR) with denominator of transferred embryos was also inappropriate as the only denominator of interest is the human subject fate, not the embryo's. The outcomes of subsequent FETs were not included in the analysis either. The live birth rate (LBR), especially cumulative LBR following a single oocyte retrieval is the most relevant outcome and the ultimate goal of infertility treatment. The application of PGS helps to eliminate non-viable embryos and probably improves IR and clinical pregnancy rate per transfer, but may also lead to a decrease of transfer cycles and transferred embryos at the same time, resulting in a lower LBR per cycle or per women. Fourth, the sample size of published studies was small.

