## 9.2 Outcomes

### 9.2.1 Primary outcome

The primary outcome is the cumulative live birth rate over the (up to) 3 embryo transfers. Live birth is defined as the delivery of any viable infant at 28 weeks or more of gestation after our interventions, and cumulative live birth rate is calculated by dividing the number of women achieving live birth after transfers of all euploid embryos in the PGS group or 3 blastocysts in the IVF group within 1 year after randomization, by the total number of women randomized to the specific group.

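### The per-protocol set drops PGS women with no euploid embryo, which moves that secondary comparison about 4 points toward PGS when there is no true difference

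*Combined protocol and SAP*

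**What the plan says.** Section 9.5 is clear about the main analysis: "The primary analysis will be performed in accordance with the principle of intent-to-treat". Section 9.2.1 matches it, dividing the number of women with a live birth "by the total number of women randomized to the specific group". A PGS woman with no euploid embryo therefore counts as a failure in the primary result.

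The secondary analysis in Section 9.5, repeated in the statistical statement at the front of the document, is called per-protocol and is defined differently: "The primary and secondary outcomes will be compared according to actual treatment that subjects received and among subjects who complete embryo transfer(s".

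Two other sections decide who falls outside that set. Section 6.2.3 ends participation when "no euploid embryo is obtained in patients assigned to the PGS group after NGS test". Section 5.1.3 keeps mosaic embryos frozen and untransferred.

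The closing text headed Final statistical analysis adds secondary analyses of "the initial, secondary and third embryo transfer in PGT-A and IVF groups", and Sections 9.2.3 and 9.5 plan comparisons after the first transfer. None of these states a denominator.

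**The concern.** A per-protocol set should leave out women whose management departed from their allocation. A PGS woman with no euploid embryo did not depart from it: her embryos were biopsied, sequenced and handled as planned. Her lack of a transfer is an outcome of PGS that arises after randomisation. Excluding her removes only failures, and almost only from one arm.

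The protocol's background section on the limitations of published trials makes a related argument. It says that "the only denominator of interest is the human subject fate". That sentence is aimed at implantation rates per embryo, so it is not an exact match. The same section also faults analysis per transfer cycle rather than per woman, and warns that PGS may raise rates per transfer while lowering the rate per woman.

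Two things are at stake. First, the restriction covers secondary outcomes too. The Good Birth Outcome, for which Section 1.2 hypothesises a PGS advantage, is inflated by the same factor. Second, this is the only planned analysis that could show the effect of crossover, which Section 5.1.4 allows and expects in fewer than 5% of subjects. If the set also loses about 6% of the PGS arm for having no euploid embryo, a difference from intention-to-treat cannot be read as an effect of crossover.

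**Working it through.** **The plan's own figure.** With 65% in both arms, a 7-point margin, one-sided 5% and 80% power, n = (1.645 + 0.842)² × 2 × 0.65 × 0.35 / 0.07² ≈ 574.1, rounded up to 575 per arm, as stated. Then 575 × 1.05 = 603.75, rounded up to 604 per arm, or 1208 in total, as stated. The planning difference on the all-randomised denominator is 65% − 65% = 0.

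**Inputs.**
- Live birth rate: "It is estimated the cumulative live birth rate after 3 single embryo transfers is 65% in each group" (Synopsis).
- Euploidy about 60% (Section 2.1), with three blastocysts sequenced (Section 3).
- Other values: aneuploidy 34.15%, 36.1% and 44.9% (Section 2.2); euploidy 40% to 56% in top-scoring blastocysts (rationale for morphologic scoring).
- Thaw survival 95% (Section 7.1, Table 5).
- Assumption: a woman's embryos are independent.

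**Formulas.** With euploidy rate e, the share of PGS women with no euploid embryo is P0 = (1 − e)³. They contribute no live births, so the PGS rate among the remaining women is 0.65 / (1 − P0).

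**At 60%.** P0 = 0.4³ = 6.4%, about 39 of 604 women. The PGS rate becomes 0.65 / 0.936 = 69.4%. The IVF rate stays at 65%, because the chance of losing all three embryos at thaw is 0.05³ = 0.0125%. The apparent difference is +4.4 points.

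| Euploidy | P0 | PGS rate in the set | Shift (points) |
|---|---|---|---|
| 65.85% | 4.0% | 67.7% | +2.7 |
| 63.9% | 4.7% | 68.2% | +3.2 |
| 60% | 6.4% | 69.4% | +4.4 |
| 56% | 8.5% | 71.1% | +6.1 |
| 55.1% | 9.1% | 71.5% | +6.5 |
| 40% | 21.6% | 82.9% | +17.9 |

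The last row is a poor guide. Holding the PGS arm at 65% with 40% euploidy requires 1 − (1 − 0.4p)³ = 0.65, so p ≈ 74% live births per euploid transfer. At 60% euploidy the same equation gives p ≈ 49%.

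**Sensitivity to independence.** With beta-binomial euploidy at mean 60% and an assumed within-woman correlation of 0.05, P0 = 7.9% and the shift is about +5.5. At 0.10, P0 = 9.4% and the shift is +6.7. Positive correlation enlarges the shift.

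**Sensitivity to thaw loss in the PGS arm.** If 95% survival is also applied there, P0 = (1 − 0.6 × 0.95)³ = 8.0% and the shift is +5.6.

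**Chance of a spurious advantage.** With 604 randomised per arm, 60% euploidy and no true difference, SE = √(0.694 × 0.306 / 565 + 0.65 × 0.35 / 604) = 0.0274. A 95% interval excludes zero in favour of PGS with probability Φ(0.0444 / 0.0274 − 1.96) ≈ 37%. The figure is about 21% at 63.9% euploidy and 66% at 55.1%.

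**Transfer-by-transfer results.** If the first-transfer denominator were women transferred, the shift at 60% euploidy would be p × 0.064 / 0.936, where p is the rate per woman randomised. The documents give no p. An assumed 40% to 55% gives +2.7 to +3.8 points. For second and third transfers no shift can be derived. The selection is plain, though: only about 0.6³ = 21.6% of PGS women would have three euploid embryos, while essentially every IVF woman starts with three blastocysts.

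**The case against.** The strongest reply is that nothing decisive rests on this set. The primary analysis uses all women randomised, and the Final statistical analysis applies the non-superiority test to the primary hypothesis only. This stands. A reader might set the 4.4 points against the 7-point margin and infer that the main conclusion is at risk, or that the per-protocol result must agree before non-superiority is claimed. The margin is set for the primary comparison ("We set a non-superiority margin at an absolute difference of 7% to retain approximately 90% of the clinical effect of the control group"), and no passage applies it to the per-protocol set or makes that set co-primary. Nor could the shift create a false non-superiority claim: it favours PGS, which makes non-superiority harder to show.

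The wording is also open to other readings. The sentence may describe two comparisons, one by treatment received and one among completers. The first would keep biopsied women with no euploid embryo, and the Final statistical analysis mentions only the first. But it does not withdraw the restriction in Section 9.5, and the Summary of changes mentions only the confidence interval.

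*Complete* could also mean finishing all study transfers. IVF women have up to three transfers to fit into one year, with a three-month wait after a pregnancy loss, so unfinished IVF women would be dropped too and the net bias is unclear. That weakens the 4.4-point figure but not the objection to the set. A woman with no transfer completes none on either reading, and the set is still selected by events after randomisation.

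A reader might also infer that the transfer-by-transfer analyses use only women transferred and carry the same 4-point shift. The documents state no denominator there, and the figure belongs to the cumulative per-protocol rate.

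Finally, Section 5.1.3 lets embryos with amplification failure be transferred, so P0 is slightly overstated. The documents give no failure rate.

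**Conclusion.** The concern holds for the secondary per-protocol analysis. Read as requiring at least one transfer, the definition removes protocol-adherent PGS failures with almost no IVF counterpart. A true zero difference in cumulative live birth becomes about +4.4 points toward PGS, or about +3 to +6.5 across most of the protocol's euploidy values. This rests on 65% in each arm and independent embryos. Under the all-transfers reading the direction is uncertain, but the comparison is still not between randomised groups.

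The consequence is a possible spurious PGS benefit in secondary results, or a conflict with intention-to-treat produced by the denominator alone. The primary analysis and its decision rule stand. For the transfer-by-transfer analyses the finding is only that the denominators are missing. The weight is moderate.

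**What to change.** Define the per-protocol set as women managed by their allocated strategy. Keep in it, as having no live birth, PGS women with no euploid embryo and women in either arm whose study embryos did not survive thaw. Exclude only real departures such as crossover, and list them in advance. Say whether the as-treated comparison is separate, and make Section 9.5 and the Final statistical analysis agree.

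Use all women randomised as the denominator for first-transfer results and for live birth accumulated by transfer number. Label second- and third-transfer rates as descriptive.

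The cost is a few lines of SAP wording and the re-programming of one population. No new data are needed, because Section 6.2.2 already records the sequencing result for each tested blastocyst.
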